###### Metabolic pathway analysis

2.9.3.2.5

The primary mass spectra (MS1) and secondary mass spectra (MS2) information of the metabolites were matched with the metabolites in the HMDB database (http://www.hmdb.ca), KEGG database (http://www.genome.jp/kegg) and METLIN database for identification. The mass error was set to 10 ppm for MS1 and 15 ppm for MS2. MetaboAnalyst 4.0 software was used for the enrichment analysis of metabolic pathways in insomnia based on the KEGG database.

### Adverse events and safety assessment

2.10

All subjects will be evaluated for safety before and at the end of treatment, and adverse events(AEs) during treatment will be recorded in a timely manner, including local haematomas, needle fainting and stagnation. Subjects will undergo a thorough history review and physical examination prior to treatment to rule out contraindications to the use of electroacupuncture, such as bleeding disorders, severe heart disease, etc. The treating acupuncturist will be rigorously trained in proper electroacupuncture techniques and emergency management, and have extensive clinical experience. In addition, the acupuncturist will check the electroacupuncture before using it to ensure that the electroacupuncture instrument used is working properly, that there are no abnormal alarm messages, and that the electrodes and wires are not damaged. Once subjects are found to have serious discomfort or suspected serious AEs, electroacupuncture treatment will be stopped immediately. First aid equipment and medication are available at the study site, and emergency contact will be established with the hospital emergency department in the first instance so that subjects can be quickly transferred for professional treatment. Serious AEs will be reported immediately to the principal investigator, and we will determine their causes and analyze their relevance to acupuncture in order to assess their impact on subject safety and the need to adjust the study protocol. Long-term follow-up will be arranged for subjects who experience serious AEs to monitor the recovery of their health status.

Safety evaluation was performed according to the grading of adverse reactions: Grade 1: safe, without any adverse reactions; Grade 2: relatively safe, if there are adverse reactions, the treatment can be continued without any treatment; Grade 3: there are safety problems, with moderate adverse reactions, the treatment can be continued after doing treatment; Grade 4: the trial was discontinued due to adverse reactions.

### Quality control

2.11

PSQI, ISI, HAS, FSS, HAMA, HAMD, and MoCA scales will be evaluated by professionally qualified physicians. Standard operating procedures and quality control procedures for serum metabolomics using UPLC-Q/TOF-MS and UPLC-QQQ-MS/MS will be established, and the data will be analyzed and processed by professional instruments to ensure the accuracy of the data. The investigators signed an investigator’s declaration, received training on the trial procedure, and had their quantitative criteria for symptoms and indications validated for consistency prior to the project’s launch. In order for the subjects to cooperate with the experiment and completely grasp its requirements, the investigator must properly carry out the informed consent process. The needle counting method was used to monitor the subjects’ needle compliance. Compliance = (actual number of needles/supposed number of needles) × 100%. Compliance <80% or >120% was considered a major violation of the trial protocol.

### Data management

2.12

Data will be recorded in paper form on the CRF by the assessor. All raw data will be kept in the Affiliated Hospital of Nanjing University of Traditional Chinese Medicine under the supervision of the Ethics Committee of the Affiliated Hospital of Nanjing University of Traditional Chinese Medicine. In order to guarantee that the data records are accurate, timely, comprehensive, and truthful, the investigators must write the study medical records concurrently with treating the individuals. For data reporting using e-CRF, a person will be designated as the “e-CRF entry officer”, who will be responsible for the initial review of the study charts and logging in to fill out the e-CRF. Upon receipt of the study charts, the “eCRF entry clerk” must first review the study charts for completeness of the project records, and then file two copies of the eCRF. The researcher will collect the data and create a database that will summarize and analyze the data recorded in the study charts to generate the conclusions and the report of the study. Upon completion of the study, the database will be locked for security purposes. Participants’ personal information will be considered confidential. Documents related to quality control, such as original records of data consistency checks, numerical range and logic checks, and blinded audits, will be retained.

### Statistical analysis

2.13

In this study, the software SPSS25.0 was first used to process the experimental data, and the measurement data were expressed by `x ± s, and the count data were expressed by the rate or the constitutive ratio. Comparison of the measurement data between the two groups was firstly analyzed by normality analysis, a t-test was used for the measurement data that conformed to normality and chi-square, and a non-parametric rank-sum test was used for the measurement data that did not conform to the normal distribution; chi-square or Fisher’s exact probability method was used for the count data. p<0.01 was taken as the difference was significant; p<0.05 was taken as the difference was statistically significant between the two groups.

### Trail Status

2.14

Protocol: version 2.0, 5/6/2024. Subjects are currently being recruited for this study.

## Discussion

3

The present study is a single-center, double-blind, clinical trial aimed at assessing the efficacy of electroacupuncture using a combined metabolomics scale and exploring the possible efficacy mechanisms and related metabolic pathways of electroacupuncture in the treatment of insomnia.

Metabolic processes and sleep are intimately associated, and both are present in all living things. Sleep disorders and deprivation can have an impact on metabolism since sleep controls bodily activities and is necessary to maintain a normal metabolism. According to recent study, insomnia can cause metabolic dysregulation by impairing insulin sensitivity, glucose tolerance, and energy balance, as well as by causing inflammation (23). According to research on animals, persistent stress-induced sleeplessness in mice results in the activation of orexin neurons in the lateral hypothalamus, which leads to hyperphagia and a decrease in the leptin/growth factor-releasing peptide ratio (24). On the other hand, mice fed a high-fat diet and subjected to prolonged stress have higher levels of free fatty acids and glucose in their blood, as well as more metabolic dysfunction including aberrant glucose tolerance (25). In addition, it was found that insomniac Drosophila showed elevated dopamine concentrations as well as elevated levels of triglycerides, cholesterol, and free fatty acids (26). The aforementioned research all point to a tight connection between metabolic abnormalities and the etiology of insomnia. In line with the hyperarousal theory of insomnia, clinical research has also revealed a 6-9% rise in 24-hour metabolic rate in patients with insomnia compared to healthy people (27).Additionally, an enlarged hypothalamic-pituitary-adrenal (HPA) axis can lead to food cravings and overeating, which can worsen the condition of the axis and raise the risk of developing other metabolic disorders such obesity, diabetes, and hypertension (28). Therefore, discovering the physiological and molecular processes involved in sleep regulation and metabolic balance can play an essential role in enhancing sleep and metabolic function in individuals.


There are some limitations of this study. First, the follow-up period of this study was short due to limited conditions. However, because most insomnia patients have a long duration of illness and are difficult to cure, it is necessary to observe the long-term effects of acupuncture on regulating metabolism and improving sleep quality. Secondly, the research employed a single-center design, which may introduce experimental bias and result in a single sample that lacks representativeness. More influencing factors should be considered and the results should be further validated and explored in a large sample population. Finally, the serum collected from subjects in this study was not fasting serum and may be affected by more factors, which may lead to bias and thus affect the results. Therefore, further metabolic studies with multicenter, large samples and extended follow-up periods are needed in the future.

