**Methods:**

A single-center, double-blind, clinical trial was the study’s design. For this study, a total of 99 participants were enrolled, and they will be split into two groups: one for insomnia and the other for health. There are 33 healthy people in the healthy group and 66 insomnia patients in the insomnia group. Acupuncture treatment will be administered to the intervention group three times a week for four weeks, for a total of twelve treatments, and will be followed up for 3 months. A combination of UPLC-Q/TOF-MS and UPLC-QQQ-MS/MS was used to qualitatively and quantitatively examine the serum of 99 participants. The Pittsburgh Sleep Quality Index (PSQI) and serum metabolomics provided the primary findings. The Insomnia Severity Index (ISI), Hyperarousal Scale (HAS), Fatigue Feverity Scale (FSS), Hamilton Depression Scale (HAMD), Hamilton Anxiety Scale (HAMA), Sleep Diary and The Montreal Cognitive Assessment (MoCA) were the secondary outcomes. For the insomnia group, serum will be collected at baseline, at the end of treatment, and the scale will be collected at baseline, after 4 weeks of treatment, and at 3 months of follow-up. For the healthy group, serum will be collected at baseline.

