##### Inclusion criteria for healthy people

2.2.2.2

Normal blood count, liver function, kidney function, electrocardiogram, blood glucose, and blood lipid after consultation and health examination; healthy, no previous organic or functional diseases or psychiatric disorders;Be in the age range of 18 to 60;not recently participated in other clinical studies;Voluntarily participate in this trial, agree to and sign the informed consent form.

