##### Requirements for blood sample collection

2.9.1.1

No caffeinated beverages or food (e.g., tea, chocolate, coffee, cola, etc.), no alcohol, and no food containing cheese and preservatives for 24h until sampling is completed;Avoid strenuous physical exercise for 24 hours before blood collection until sampling is completed;Avoid emotional stress on the day of blood collection and rest for at least 5 minutes before blood collection;Female subjects should avoid menstruation.

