##### Collection and storage of blood samples

2.9.1.2

Venous blood was collected from the subjects, whole blood was collected in serum tubes, and the volume of blood collected was about 4mL, centrifuged at 4°C, 3500r/min for 10min. The upper layer of clear serum was extracted with a pipette gun to 400μL into 1.5ml graduated EP tubes with pointed bottoms, and then placed in a refrigerator at -80°C for storage and preparation for examination.

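### Serum metabolomics is a primary outcome measured on non-fasting blood, and the stated sampling rules and analysis do not control meal state or time of day

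*Protocol article*

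**What the plan says.** The abstract and section 2.8.1 make serum metabolomics a primary outcome together with PSQI. On timing, the abstract says "For the insomnia group, serum will be collected at baseline, at the end of treatment"; section 2.8.3 has the healthy group sampled once, at enrolment.

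Section 2.9.1.1 lists the conditions for a draw. It bans caffeine for 24 hours, together with "no alcohol, and no food containing cheese and preservatives for 24h until sampling is completed", and also restricts strenuous exercise for 24 hours. Participants are told: "Avoid emotional stress on the day of blood collection and rest for at least 5 minutes before blood collection". Women are to avoid menstruation. The list contains no fasting interval, standard meal, time since last meal or clock time. Section 2.9.1.2 describes the draw itself without a time of day: "Venous blood was collected from the subjects, whole blood was collected in serum tubes, and the volume of blood collected was about 4mL".

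The limitations paragraph of the Discussion then says that "the serum collected from subjects in this study was not fasting serum and may be affected by more factors", and goes on to accept that bias may follow and that the results may be affected. Its only response is to call for further studies.

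The multivariate analysis section screens metabolites by VIP>1 and a univariate two-sided p<0.05. It names no adjustment for meal state or sampling time.

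**The concern.** Two comparisons carry the metabolomic conclusions: insomnia (Group A) against healthy volunteers, and insomnia patients before against after treatment. Randomisation protects neither. It only assigns patients to assay Group A or B, every patient receives the same electroacupuncture, and there is no untreated insomnia arm.

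The Introduction cites earlier work that places insomnia-related changes in amino-acid, neurotransmitter and glycolipid metabolism. Several of these are pathways that recent food intake can also move. If meal state or hour of draw differs on average between healthy volunteers and patients, the difference can be read as a marker of insomnia. If it differs between the baseline and week-4 visits, it can be read as the reversal that the Discussion intends to use as proof of mechanism.

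The planned cross-check would not expose this. Group B is a second set of patients measured on a second platform, but their blood is drawn under the same rules. A systematic difference affecting all patients would recur there and look like confirmation.

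If meal state varies only at random, the harm is smaller: more variance and lower power.

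**Working it through.** **The plan's own figure.** The only sample-size calculation concerns PSQI (section 2.3): effect size 0.8, α=0.05, power 0.9, giving 52 insomnia and 26 healthy. A two-sample t-test, two-sided, with 2:1 allocation, has noncentrality 0.8 × √(52×26/78) = 3.33 on 76 df and power 0.908, so 52/26 reproduces. It says nothing about metabolites. The article gives no metabolite variance and no meal-related variance, so everything below rests on assumed inputs.

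**Inputs.** 33 healthy; 66 insomnia patients split 1:1, hence 33 in Group A; screening p<0.05, two-sided. No drop-out is assumed. The VIP>1 filter is not modelled, so the rates below are univariate rejection rates, not rates of declared markers.

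**1. Bias, Group A v healthy.** Suppose a metabolite has no true difference, but unequal meal state or draw time shifts its mean by b SD. The noncentrality is b × √(33/2) = 4.062b on 64 df, with critical value 1.998.

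| Assumed shift b (SD) | Noncentrality | P(p<0.05) |
|---|---|---|
| 0 | 0 | 5.0% |
| 0.2 | 0.81 | 12.6% |
| 0.25 | 1.02 | 17.0% |
| 0.3 | 1.22 | 22.5% |
| 0.5 | 2.03 | 51.6% |

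**2. Bias, before v after, 33 pairs.** With within-patient correlation ρ (assumed), the noncentrality is b × √33 / √(2(1−ρ)) on 32 df, with critical value 2.037. At ρ=0.5 this is b × 5.745.

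| Assumed shift b (SD) | ρ=0.3 | ρ=0.5 | ρ=0.7 |
|---|---|---|---|
| 0.2 | 15.6% | 20.0% | 30.1% |
| 0.3 | 29.3% | 38.7% | 57.8% |
| 0.5 | 65.3% | 79.5% | 94.9% |

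At positive correlations above 0.5 or so, and already at the values shown, pairing does not protect against a shift between visits. It removes stable patient differences and so makes the same shift easier to detect.

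**3. Noise only.** Suppose a share f of total metabolite variance is random meal or time variation, and the true difference is 0.8 SD without it. The 0.8 is borrowed from the PSQI calculation purely as an illustration. The effective difference is 0.8 × √(1−f).

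| Assumed f | Effective d | Power, 33 v 33 | Factor on n to hold power, 1/(1−f) |
|---|---|---|---|
| 0 | 0.800 | 0.893 | 1.00 |
| 10% | 0.759 | 0.859 | 1.11 |
| 20% | 0.716 | 0.817 | 1.25 |
| 30% | 0.669 | 0.764 | 1.43 |
| 50% | 0.566 | 0.619 | 2.00 |

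In this noise-only case the false-positive rate stays at 5%.

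**The case against.** The strongest reply is that this is disclosed. The authors name non-fasting serum and its bias risk, and the article contains no contradiction or wrong figure on the point. That is right, and it makes this a weakness of design rather than a hidden error. Disclosure does not control the effect, however, and recruitment is still open, so control is possible.

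Second, non-fasting blood is compatible with a fixed sampling slot. Section 2.11 promises standard operating procedures for the metabolomics, whose content is not shown, and a condensed article may leave a time window to them. This stands in part: the supportable statement is that no common meal state or window is stated, not that none exists.

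Third, a reader might infer that healthy volunteers and patients are drawn in different meal states, because the healthy criteria require "Normal blood count, liver function, kidney function, electrocardiogram, blood glucose, and blood lipid after consultation and health examination". The article does not support that. It does not say that the examination is done fasting or that study serum is taken at it. The non-fasting statement covers the study's subjects without exception, and insomnia patients are also recruited through the Physical Examination Center. No documented mechanism makes meal state differ between groups or visits.

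Fourth, the percentages are set by the chosen shifts and correlations. That is correct, and they are illustrations only.

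**Conclusion.** The point holds as an uncontrolled source of variation in a primary outcome. The serum is non-fasting by the authors' own account, the stated sampling rules fix neither meal state nor hour, the described analysis does not adjust for them, and neither key comparison is randomised.

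A reader might go further and conclude that the metabolomic results are biased. The documents do not support that. Bias requires a systematic difference between groups or visits, which is possible under the stated rules but not shown.

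The true size cannot be computed from the article. Under the assumptions above, a modest shift of 0.2 to 0.25 SD would raise the univariate false-positive rate from 5% to between 13% and 17% for Group A v healthy, and a 0.2 SD shift would raise it to 20% for before v after at correlation 0.5. A 0.5 SD shift would raise the rates to 52% and 80%. The change should be made, with medium confidence.

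**What to change.** Amend section 2.9.1.1 and the metabolomic analysis section:

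1. For all remaining draws, state one meal state and one clock-time window, the same for healthy, baseline and week-4 samples. If an operating procedure already sets these, cite it.
2. Draw each patient's week-4 sample in the same meal state and window as that patient's baseline. For patients already sampled at baseline, this takes precedence over item 1.
3. Record hours since last meal and clock time at every draw, and retrieve them for past draws where records allow.
4. Adjust the univariate metabolite comparisons for both variables, and add a sensitivity analysis limited to samples of like meal state.

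Moving later participants to an overnight fast is optional. It would mix sample types and, if the two groups enrol at different rates, could tie meal state to group. If adopted, it should start at the same time in both groups, with item 2 kept for patients whose baseline was non-fasting.

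The cost is a short amendment, two CRF fields and a minor scheduling burden, with no extra draws or participants. Earlier samples without a recorded meal time cannot be adjusted, and that limit should be reported.
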